### Patient and public involvement

A panel of eight parents was established for this trial. This panel helped to shape the grant proposal and final study protocol during online focus group meetings, with particular advice given on patient-relevant outcomes including the minimally important clinical differences, recruitment strategy and the design of data collection. The parent panel will be actively involved throughout all critical stages of the trial through regular parent panel meetings.

### Statistical analysis

All analyses will be performed according to the intention-to-treat principle and blinded with respect to study group assignment. The results will be reported in accordance with the Consolidated Standards of Reporting Trials guidelines.^30^

#### Clinical effectiveness

Descriptive statistics will be used to assess any baseline differences between treatment groups. The primary outcome will be analysed with a linear regression model with a residual covariance (ie, Generalized Estimating Equations (GEE) type) matrix to correct for repeated measurements. In main (adjusted) analysis, treatment group, time, a priori specified prognostic factors (baseline ear pain score, duration of ear pain prior to enrolment) and stratification factors (age (<2 years vs 2 years and above), AOM laterality (unilateral vs bilateral) and baseline antibiotic prescribing (yes vs no)) will be included in the model. The validity of the model, that is, normality and homoscedasticity, will be evaluated by assessing residuals and the comparison between treatment groups will be expressed as differences in means with 95% CIs. If more than 5% of baseline and outcome data are missing, a sensitivity analysis will be performed using multiple imputation techniques.^31 32^

Secondary outcomes will be analysed using negative-binomial regression analyses for count variables, log binomial regression analyses for dichotomous variables and linear regression analyses for continuous variables, where applicable, adjusted for repeated measurements. For these analyses, the comparison between treatment groups will be expressed as rate ratios, risk ratios and mean differences, respectively, all with 95% CIs.

We will also conduct prespecified, exploratory subgroup analyses to investigate whether age (<2 years vs 2 years and above) or AOM laterality (unilateral vs bilateral) modifies the effectiveness of analgesic ear drops. In further sensitivity analysis, we will also explore the added impact of antibiotic consumption on the primary outcome of interest.

#### Cost-effectiveness analysis

Alongside the trial, a cost-effectiveness analysis from a societal perspective, that is, including both medical and non-medical costs, will be performed. The societal perspective is particularly relevant in this case, since non-medical costs are particularly relevant in AOM.^33^ Those costs mainly relate to parental productivity losses and costs of additional childcare.

#### Cost analysis

All costs will be estimated at the patient level. Costs of medication use will be retrieved from the Dutch formulary and a pharmacist’s fee will be added for every prescription.^24 34^ Costs of OTC and complementary medicines will be calculated per day, based on current average retail prices. Costs of consulting a GP or a medical specialist, and costs of hospitalisation will be based on current Dutch guidelines for pharmaco-economic evaluation in healthcare research. Costs of diagnostic tests will also be derived from these guidelines.^34 35^ Costs of surgical procedures will be retrieved from a previous Dutch costing study that calculated costs for the different components of surgical procedures.^36^

Resource use such as doctor’s visits, prescribed medication (including antibiotics), specialist referrals, hospital admissions, surgical interventions as well as out-of-pocket expenses such as OTC medication, child care and travel costs will be collected from study diaries filled out by parents. Cost prices will be estimated according to guidelines for pharmaco-economic evaluation in healthcare research.^34 35^ Costs associated with productivity losses will be retrieved from the iPCQ Questionnaire and estimated using the friction cost method.^29 37^ The hourly cost estimate for childcare will be derived from the Dutch National Institute for Family Finance Information.^38^ Travel expenses will be calculated for healthcare visits following the Dutch guideline for economic evaluation.^35^ Mean costs per patient will be compared across the randomisation groups. As the time horizon is only 4 weeks, discounting does not apply.

#### Cost-effectiveness results

Costs from a societal perspective will be compared with the parent-reported ear pain scores over the first 3 days. We will calculate incremental cost-effectiveness ratios by dividing the estimated differences in costs between groups by the differences in effects observed, that is, the additional cost per additional 1-point reduction in mean ear pain score over the first 3 days for the analgesic ear drops group versus the usual care group. Uncertainty will be addressed by means of two-stage non-parametric bootstrap sampling. The effect of any difference in baseline characteristics on cost-effectiveness results will be investigated using net benefit regression methods. In case of missing data, we will use multiple imputation techniques. The final results will be presented using incremental cost-effectiveness planes and cost-effectiveness acceptability curves.

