**Methods and analysis:**

This is a pragmatic, two-arm, individually randomised, open, superiority trial with cost-effectiveness analysis and nested mixed-methods process evaluation in general practices in the Netherlands. We aim to recruit 300 children aged 1–6 years with a general practitioner (GP) diagnosis of AOM and ear pain. Children will be randomly allocated (ratio 1:1) to either (1) lidocaine hydrochloride 5 mg/g ear drops (Otalgan) one to two drops up to six times daily for a maximum of 7 days in addition to usual care (oral analgesics, with/without antibiotics); or (2) usual care. Parents will complete a symptom diary for 4 weeks as well as generic and disease-specific quality of life questionnaires at baseline and 4 weeks. The primary outcome is the parent-reported ear pain score (0–10) over the first 3 days. Secondary outcomes include proportion of children consuming antibiotics, oral analgesic use and overall symptom burden in the first 7 days; number of days with ear pain, number of GP reconsultations and subsequent antibiotic prescribing, adverse events, complications of AOM and cost-effectiveness during 4-week follow-up; generic and disease-specific quality of life at 4 weeks; parents’ and GPs’ views and experiences with treatment acceptability, usability and satisfaction.

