## Introduction

Although the current COVID-19 pandemic has a profound influence on the incidence of acute otitis media (AOM) in children,^1–3^ it will remain an important cause of primary care consultations.^4 5^ Ear pain is the predominant symptom and central to children’s and parents’ experience of the condition.^6 7^ High-quality studies have shown that most symptoms of AOM settle within a few days without antibiotics in otherwise healthy children living in high-income countries,^8^ but it may take 8 days for ear pain to fully resolve in 90% of the children.^9^ Globally, most AOM clinical practice guidelines therefore recommend oral analgesics in all, and antibiotics in selected, children.^10^ However, antibiotics are frequently prescribed in children with AOM,^4 5^ leading to side effects in at least 1 out of 10 children and emergence of antimicrobial resistance.^11 12^ Evidence of effectiveness of management options to relieve the most distressing symptom of AOM and reduce reliance on antibiotics is therefore urgently needed.^13^

Recently, we found that a general practitioner (GP)-targeted educational intervention to improve pain management in children with AOM resulted in an increase in oral analgesic use, in particular ibuprofen, but failed to reduce parent-reported ear pain and antibiotic use.^14^ Therefore, alternative interventions need further exploration. Analgesic ear drops, widely available, cheap and safe, may be well suited to fill this gap. When applied into the external auditory canal, these agents could relieve pain and distress by blocking nerve conduction of the tympanic membrane.^15^ So far, evidence on their use in children with AOM is limited.^15 16^ Our trial aims to produce this important evidence.

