#### Study group assignment

At the conclusion of the home visit, a trial randomisation website will be accessed for concealed study group assignment. An independent data manager generates a computer-generated randomisation sequence stratified for age (<2 years vs 2 years and above), AOM laterality (unilateral vs bilateral) and AOM baseline antibiotic prescribing (yes vs no). Children will be randomly allocated to either (1) lidocaine hydrochloride 5 mg/g (Otalgan) ear drops one to two drops up to six times daily for a maximum of 7 days^24^
^25^ with usual care (oral analgesics, with/without antibiotics); or (2) usual care. Analgesic ear drops will be provided by the study team. These drops should not be used in children with a tympanic membrane perforation or ventilation tube as they carry a risk of inner ear damage causing hearing loss or tinnitus. These children will therefore be excluded, as well as those with ear wax obscuring visualisation of the tympanic membrane. Parents of children allocated to the intervention group are expressly instructed to stop applying the drops if their child develops ear discharge.

The study team will notify the GP about the result of the randomisation. The local pharmacist will be notified in case the child is allocated to the analgesic ear drops, in order to check any known sensitivities/allergies and any interactions (with current or future drugs). Any treatment decisions other than the use of analgesic ear drops, that is, antibiotics and oral analgesics, will be left to the GP’s discretion in both groups. To those allocated to the intervention group, the study physician will not provide any treatment advice other than instructions about the use of analgesic ear drops. To those allocated to the control group, the study physician will not provide any treatment advice.

During follow-up, parents and GPs will be encouraged to manage AOM symptoms according to current clinical practice guidance on AOM in children issued by the Dutch College of General Practitioners. Lidocaine ear drops are currently not recommended in this guideline due to the lack of evidence.^23^

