#### Secondary outcomes

Proportion of children consuming antibiotics in the first 7 days.Oral analgesic use in the first 7 days.Overall symptom burden (crying/distress, disturbed sleep, interference with normal activity, appetite, fever and hearing problems) using a 0–6 Likert scale in the first 7 days.Number of days with ear pain during follow-up (4 weeks).Number of GP reconsultations with/without subsequent antibiotic prescribing during follow-up.Adverse events during follow-up.Complications of AOM during follow-up.Costs and cost-effectiveness during follow-up.Generic quality of life of the child at 4 weeks.Disease-specific quality of life of the child at 4 weeks.Parents’ and GPs’ views of treatment acceptability, usability and satisfaction.

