Our trial aims to do so by assessing the clinical and cost-effectiveness of analgesic ear drops in children with AOM, as well as views and experiences of parents and GPs through the nested process evaluation. The pragmatic, open design enhances the applicability of the trial findings to daily practice and is most suited to address the key secondary outcome of the impact of the analgesic ear drops on the proportion of children consuming antibiotics in everyday practice.^39^ This would be much more difficult to determine realistically in a placebo-blinded study where children in both groups would receive ear drops (either placebo or analgesic drops); such ‘treatment’ may in itself lead to altered parental (healthcare seeking) behaviour. Additionally, the open design, in which the control group receives usual care, is most suited for ‘real-world’ cost-effectiveness analysis. However, the lack of blinding in combination with the subjective, parent-reported outcomes might also lead to bias in the assessment of analgesic effects. To minimise this potential bias, the study physician will emphasise during the baseline visit that it is not known whether the drops have any effect in children with AOM. Furthermore, a recent meta-epidemiological study found no evidence for a difference in estimated treatment effect between blinded and non-blinded trials.^40^ Although it is still unclear what caused the results of this study, it suggests that blinding is less important than anticipated. Our design does not control for the placebo effects, but will more closely reflect the benefits that would accrue in everyday practice with regard to analgesic effects.

Although not recommended in the Dutch AOM clinical practice guideline,^23^ the OTC availability of lidocaine ear drops may inherently incur the risk of contamination, that is, parents in the control group buying lidocaine ear drops themselves. We consider this unlikely since only 5% (10 of 221) of participants did use lidocaine ear drops in our previous trial of a GP-targeted educational intervention to improve pain management in children with AOM.^14^ We will, however, capture data on the use of lidocaine ear drops in all trial participants to monitor potential contamination.

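### The cost-effectiveness ratio sets 4-week costs against a pain effect that ends at day 3, with no ratio on the same horizon as the costs

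*Protocol article*

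**What the plan says.** All references are to the protocol article.

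- **Outcome horizon.** Secondary outcomes lists "Costs and cost-effectiveness during follow-up", and the abstract gives the period: "complications of AOM and cost-effectiveness during 4-week follow-up". The Discussion names "assessing the clinical and cost-effectiveness of analgesic ear drops in children with AOM" as something the trial aims to do, without a horizon. The strengths and limitations box counts cost-effectiveness among the key secondary outcomes.
- **Cost horizon.** Cost analysis states: "As the time horizon is only 4 weeks, discounting does not apply". Resource use comes from the parents' diary, which runs for 4 weeks. Productivity losses come from a questionnaire completed at 4 weeks.
- **Effect horizon.** Cost-effectiveness results states: "Costs from a societal perspective will be compared with the parent-reported ear pain scores over the first 3 days". It defines the ratio as "the additional cost per additional 1-point reduction in mean ear pain score over the first 3 days". The article names no other effect measure for the economic analysis.
- **Pain and treatment after day 3.** The Introduction says of natural history that "it may take 8 days for ear pain to fully resolve in 90% of the children". Study group assignment permits the drops at "one to two drops up to six times daily for a maximum of 7 days".

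**The concern.** A ratio presented as cost-effectiveness over 4 weeks should set costs and effects over the same period, or explain why it does not. Here the numerator runs for 4 weeks and the denominator stops at day 3, although the article itself expects some children to have pain, and to use drops, after that day.

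If relief continues beyond day 3, the extra relief is not credited as an effect. If the usual-care children catch up, or pain returns in the drops group, that is not debited. Costs from those later days are counted either way. The cost-effectiveness planes and acceptability curves are built on the same pairing, so they carry the same limitation. At stake is how a key secondary conclusion is read. The primary analysis is not affected.

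**Working it through.** **1. The horizons side by side.**

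| Element | Period | Section |
|---|---|---|
| Cost-effectiveness outcome | 4 weeks | Abstract; Secondary outcomes |
| Costs | 4 weeks | Cost analysis |
| Effect in the ratio | 3 days | Cost-effectiveness results |
| Permitted drop use | up to 7 days | Study group assignment |
| Pain resolved in 90% of children | may take 8 days | Introduction |

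The effect window is 3/28 = 11% of the cost horizon and 3/7 = 43% of the maximum period of drop use.

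**2. The plan's own figure for the 3-day effect.** Sample size calculation gives a usual-care mean of 4.36 (SD 2.12) over the first 3 days, a 20% reduction, 90% power and alpha 0.05 (taken as two-sided).

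- Difference: 0.20 × 4.36 = 0.872, stated as 0.87.
- Normal approximation: n = 2 × (1.96 + 1.28)² × (2.12/0.87)² ≈ 125 per group.
- t-test version: 125.75, rounded up to 126, which is the stated figure.

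So 0.87 is confirmed as a difference in the 3-day mean. Nothing in the sample size is contested.

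**3. What the 3-day window could leave out.** The article gives no effect after day 3, so this step is an assumption shown as a range. Let the difference be 0.87 points per day on days 1 to 3, and f × 0.87 on days 4 to 7 (the rest of the permitted drop use), with nothing after day 7.

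- 3-day gain: 3 × 0.87 = 2.61 point-days.
- 7-day gain: 2.61 + 4 × f × 0.87 = 2.61 + 3.48f.
- Share omitted: 1 − 2.61/(2.61 + 3.48f).
- Overstatement of cost per point-day for the same 4-week cost difference: (2.61 + 3.48f)/2.61.

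| f | 7-day gain (point-days) | Share omitted | Overstatement factor |
|---|---|---|---|
| 0 | 2.61 | 0% | 1.00 |
| 0.25 | 3.48 | 25% | 1.33 |
| 0.5 | 4.35 | 40% | 1.67 |
| 1 | 6.09 | 57% | 2.33 |

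A 1-point difference in the 3-day mean is 3 point-days, so the plan's ratio divided by 3 is on the point-day scale used here.

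**4. The opposite direction.** If pain is worse with drops after day 3, f is negative and the 3-day window flatters them. With f = −0.25 (again an assumption) the 7-day gain is 2.61 − 0.87 = 1.74 point-days, and cost per point-day is understated by a factor of 1.74/2.61 = 0.67. The documents do not allow a choice between these cases.

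**5. Which side can be matched.** Productivity loss is measured once, by a questionnaire at 4 weeks, so costs cannot readily be cut back to 3 days. The symptom diary, which includes ear pain scores, runs for 4 weeks, and days with ear pain over 4 weeks is already a secondary outcome. The matching has to come from the effect side, and the data for it are planned.

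**The case against.** The strongest defence is that this is an open and common choice. The unit of the ratio is spelled out, the effect is the powered primary outcome, and following costs for longer captures the downstream consequences of early relief. Days with ear pain over 4 weeks will be compared between arms anyway, so catch-up or rebound affecting that count would be visible next to the costs. This supports keeping the 3-day ratio. It does not make that ratio a measure of cost-effectiveness over 4 weeks.

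A second argument is that a condensed article may leave supplementary ratios to a fuller document. That would answer a complaint about a missing sensitivity analysis. Here both horizons are fixed in the article, and they differ.

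Three stronger readings are tempting, and the objections to them stand:

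- A reader might infer that benefit after day 3 counts for nothing. It does not: fewer reconsultations, less medication or fewer lost work days later on all reduce the 4-week cost difference. Only the later pain itself is outside the ratio.
- A reader might turn the 8-day figure into a daily rate of decline in mean pain and so derive a fixed share of lost benefit. That figure is a proportion of children whose pain has resolved, not a mean score, and the same sentence says that most symptoms settle within a few days.
- A reader might want to replace the 3-day ratio with cost per pain-day avoided. A count of days ignores intensity. If drops lowered every score by 20%, a painful day would remain a painful day and no days would be avoided despite real relief.

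It is also true that if the effect persists in a fixed proportion, the ratio is only rescaled: the quadrant on the plane does not change, and the willingness-to-pay axis changes units. The article gives no threshold in either unit. But whether the effect persists in that way is what the 3-day window cannot show.

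**Conclusion.** The point holds as a mismatch of horizons that should be corrected. Cost-effectiveness is declared over 4 weeks and costed over 4 weeks, but the only effect in the ratio ends at day 3, so the ratio cannot reflect pain saved or regained afterwards.

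The size is unknown in advance. If between none and all of the 0.87-point difference persists on days 4 to 7, the 3-day window omits 0% to 57% of the 7-day pain benefit. If pain rebounds, the error runs the other way. A reader might conclude that the drops will look less cost-effective than they are; the documents do not support any direction.

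Nor is 4-week cost-effectiveness the trial's formal objective. The Objective section concerns ear pain relief only; cost-effectiveness is one of eleven secondary outcomes and an aim named in the Discussion.

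**What to change.** In Cost-effectiveness results:

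1. Keep the 3-day ratio and label it as a 3-day effect paired with 4-week costs.
2. Prespecify a co-reported ratio on the cost horizon, preferably incremental societal cost per ear-pain point-day averted over 4 weeks, that is, the area under the daily 0–10 score. This keeps intensity in the effect.
3. Add incremental societal cost per ear-pain day avoided over 4 weeks as a supplement, from the existing secondary outcome.
4. Give each added ratio its own bootstrap plane and acceptability curve.
5. State that any conclusion about 4-week cost-effectiveness will consider the matched-horizon ratio alongside the 3-day ratio.

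The cost is some added wording and a further run of the planned bootstrap on diary data. The article does not say outright that the 0–10 score is recorded every day after day 3, so this should be confirmed; if it is not, the pain-day ratio is the one available. The downside is small: more ratios to report, on outcomes with no stated power. Setting them out now avoids choosing the effect measure after the results are known.

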### Monitoring and safety

The trial will be monitored regularly by an independent research data monitor of the UMC Utrecht to ensure the quality of the trial execution. Since we do not expect any safety issues and the overall risk of this trial was judged negligible, we have not established a data safety monitoring board and refrain from conducting a safety interim analysis. However, in accordance to section 10, subsection 4, of the Medical Research Involving Human Subjects Act (WMO), the sponsor will suspend the study if there is sufficient ground that continuation of the study will jeopardise subject health or safety.

## Ethics and dissemination

The study will be conducted according to the principles of the Declaration of Helsinki (10th version, October 2013), the International Conference on Harmonisation (ICH) Good Clinical Practice E6(R2) guideline, the Dutch Law on medicinal products (‘geneesmiddelenwet’) and in accordance with the WMO. The Medical Research Ethics Committee Utrecht, the Netherlands, has approved the protocol (21-447/G-D).

Research findings will be disseminated through publications in peer-reviewed medical journals targeted towards the wider audience of health professionals involved in the care of children and presented at relevant national and international scientific meetings. We will work with our parent panel to help interpret the findings of the trial and harness their resources for dissemination to the lay public.

On completion of the trial, data will be stored for a minimum of 25 years at a central data drive at the Julius Center. We will publish the metadata in the DataverseNL repository and will provide a persistent identifier. The data will be available to researchers who provide a methodologically sound proposal to achieve the aims in the approved proposal. Proposals to gain access to the data should be directed to the principal investigator (RV). Data requestors will need to sign a data sharing agreement.

